
## Methods

### Trial design and surgical quality assurance

The INSEC study (ChiCTR1900023161) is a randomized, open-label, multicenter and non-inferiority controlled clinical trial in China. Potential participants will be patients with pathologically confirmed endometrial cancer at the Zhejiang Cancer Hospital, Jiaxing Maternity and Child Health Care Hospital, and the First Hospital of Jiaxing in China. Patients will be randomly assigned in a 1:1 ratio to two groups, Arm A and Arm B (Fig. 1). Patients in Arm A will undergo sentinel lymph node biopsy (SLNB) + total hysterectomy (TH) + bilateral salpingo-oophorectomy (BSO) ± paraaortic lymph node resection. Patients in Arm B will undergo SLNB + TH + BSO + pelvic lymphadenectomy (PL) ± paraaortic lymph node resection.

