### Statistical methods

Disease-free survival and overall survival curves will be evaluated using the Kaplan Meier method. The survival difference between the two groups will be analyzed by log-rank method. The analysis of prognostic factors will use appropriate regression models (such as Cox model). Efficacy indicators will be compared through intention-to-treat analysis including all randomized patients. Toxicity will be analyzed based on the treatment received. The 95% confidence interval of the difference between the two groups will be calculated at the same time. Descriptive statistical analysis will be used for treatment-related adverse events and quality of life scores (QLQ-C30, QLQ-CX24). The normality and equality of differences between the two groups of continuous variables will be evaluated. Discrete variables (such as presence/absence of postoperative infection) will be aggregated by frequency/proportion.

For continuous variables, analysis of variance and/or regression analysis will be used as appropriate. If the assumptions of these tests are violated, an alternative nonparametric test method will be used. Differences in discrete variables between groups will be assessed by chi square test. The risk proportional regression model will be used to explore the prognostic factors such as age, degree of differentiation, lymph node metastasis, and PS-ECOG.

The hypothesis H0: “Sentinel lymph node biopsy alone is not inferior to sentinel lymph node biopsy plus lymphadenectomy for early stage endometrial cancer with negative nodal assessment intraoperatively.”

In the current study, there are three patient groups: intention-to-treat (ITT) group, including all randomized patients who signed the consent form; a group of those in serious violation of the protocol, excluded from the efficacy analysis; and a safe population of all randomized patients who at least start the study treatment.

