### Sample size

The primary endpoint of this study is 3-year DFS. According to the results of previous research, patients with stage I endometrial cancer who received laparoscopy had 3-year DFS of 88.6% [18]. It is assumed that the 3-year DFS of the reference group and the experimental group is 88%, and the non-inferior boundary value is 8%. Considering the 20% loss of follow-up rate, 361 subjects need to be included in each group to ensure 80.0% power using a 2-sided log-rank test with a type I error rate of 0.05 to reject the null hypothesis. The total sample size of this study is 722 and the number of outcome events in each group is 40. The sample size calculation was done using the PASS software (version 11.0).

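### The null hypothesis is stated backwards for a non-inferiority trial and contradicts the power statement in the Sample size section

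*Protocol article*

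**What the plan says.** All references are to the protocol article.

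- **Trial design and surgical quality assurance:** the study "is a randomized, open-label, multicenter and non-inferiority controlled clinical trial in China".
- **Statistical methods, hypothesis:** H0 is that "Sentinel lymph node biopsy alone is not inferior to sentinel lymph node biopsy plus lymphadenectomy", in early-stage disease with negative nodes at operation. No alternative hypothesis is given.
- **Statistical methods, test:** "The survival difference between the two groups will be analyzed by log-rank method". No shift of the test by the margin is mentioned.
- **Statistical methods, interval:** "The 95% confidence interval of the difference between the two groups will be calculated at the same time". The interval is not tied to the margin.
- **Sample size:** 3-year DFS is taken as 88% in both arms, with a non-inferiority boundary of 8% and 20% loss to follow-up. The section gives 361 patients and 40 events per arm, for "80.0% power using a 2-sided log-rank test with a type I error rate of 0.05 to reject the null hypothesis".

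**The concern.** A non-inferiority claim is made by rejecting inferiority of at least the margin. The stated H0 puts the desired conclusion in the place of the null. Rejecting it would show inferiority, and failing to reject it would leave non-inferiority standing.

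Two things are at stake. First, the two sections cannot both be right. Under the stated H0, the power statement would ask for 80% power to reject non-inferiority when the arms are identical, yet a two-sided 0.05 log-rank test of equal arms rejects only about 5% of the time. Second, the only test named for DFS is the ordinary log-rank test. Someone applying the H0 literally could take a non-significant result as the favourable conclusion. Fewer events or more loss would then make that conclusion easier to reach.

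**Working it through.** **Inputs.** From Sample size: 88% in both arms, margin 8% (read as percentage points, so 80% at the margin), 361 per arm, 20% loss, 40 events per arm, alpha 0.05 two-sided, power 80%. From Visit procedures: 3 years of follow-up. Assumed here: proportional (exponential) hazards.

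**1. Which null do the plan's own figures use?**

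HR at the margin = ln(0.80)/ln(0.88) = 1.746, so ln HR = 0.557.

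Total events (Schoenfeld, 1:1) = (z_alpha + z_power)² / (0.25 × 0.557²):

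- One-sided 0.05: (1.645 + 0.842)² / 0.0776 = 79.7, so 80 events, or 40 per arm. This matches the plan.
- Two-sided 0.05: (1.960 + 0.842)² / 0.0776 = 101.2, so 102 events. This does not match.

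The 361 follows from 40 / (0.8 × 0.1385) = 361. The event probability 0.1385 corresponds to 88% at 3 years with a mean follow-up of about 3.5 years, which is my assumption. With exactly 3 years (probability 0.12) the same sum gives 417.

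So the stated event count is that of a non-inferiority log-rank design with equal arms as the alternative and inferiority at HR 1.746 as the null, at one-sided 0.05. It does not fit the H0 in Statistical methods or the two-sided test in Sample size.

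**2. What would the literal reading cost at the margin?**

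With D events and a true 80% versus 88%:

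P(non-significant, two-sided 0.05) = 1 - Phi(0.557 × √D / 2 - 1.96)

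| Scenario | D | Formula | Simulation |
|---|---|---|---|
| 361 per arm, no loss: 361 × (0.12 + 0.20) | 115.5 | 15.1% | 16.3% |
| 361 per arm, 20% exponential loss: 361 × (0.1078 + 0.18) | 103.9 | 19.0% | 19.9% |
| 289 per arm (all loss early): 289 × (0.12 + 0.20) | 92.5 | 23.6% | 25.5% |
| Analysis at the stated 80 events | 80 | 29.8% | not run |

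With 289 per arm and a mean follow-up of about 3.5 years the figure is 18.1%. With a one-sided 0.05 test the four rows become 8.9%, 11.6%, 15.1% and 19.9%.

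**3. What does a margin-based rule give?**

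Claiming non-inferiority only if the lower limit for the Kaplan-Meier difference at 3 years lies above -8 points gives a simulated false-claim rate at the margin of 2.3-2.7% with a two-sided 95% CI, and 5.2-5.3% with a 90% CI.

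Power with 88% in both arms:

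- Kaplan-Meier difference, 95% CI, 289 per arm: SE = √(2 × 0.88 × 0.12 / 289) = 0.0270; Phi(0.08/0.0270 - 1.96) = 84%.
- The same with 361 per arm and 20% exponential loss: 87% (simulation).
- Hazard-ratio scale, 80 events: Phi(0.557 × √80 / 2 - 1.645) = 80% at one-sided 0.05; replacing 1.645 by 1.96 gives 70% at one-sided 0.025.

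**The case against.** The strongest reply is that this is a mislabelled sentence. The trial is called non-inferiority, a margin is set, a 95% CI of the between-group difference is planned, and the event count reproduces as a proper non-inferiority calculation. The article also condenses a longer protocol, and a detailed decision rule may stand there or in the SAP. Most of this stands, and it limits what can be claimed:

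- A reader might infer that the trial will treat a non-significant log-rank test as non-inferiority. No section says so. It is only what the stated H0 and the stated test would permit if taken together literally.
- A reader might infer that the error rates were swapped in the design. The event count shows otherwise: the sizing used inferiority as the null.
- A reader might set the 19-24% against an intended risk of 2.5%. The document states no such target. It says two-sided 0.05, while its events match one-sided 0.05, so the intended one-sided risk could be 2.5% or 5%.
- Non-significant results for a true deficit smaller than 8 points are not false claims, because such a deficit lies inside the plan's own margin. Only the figure at the margin counts here.

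The reply does not remove the error. The point does not rest on a missing detail: the article states a primary hypothesis, states it the wrong way round, and contradicts it in the next section. No other sentence corrects it.

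**Conclusion.** The point holds as a reversed null hypothesis that conflicts with the Sample size section. This is certain from the text and affects the primary inference, so it is more than a clerical slip. That a non-significant test would be read as non-inferiority is a possibility the wording leaves open, not a rule of the plan.

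If it were read that way, the chance of a non-significant result at a true 80% versus 88% is about 19-24% by formula, given a two-sided 0.05 test, proportional hazards, 3 years' follow-up and 20% loss. Simulation runs one to two points higher. Across two-sided cases from no loss to analysis at the stated 80 events it is about 15-30%. It is lower for a one-sided test or longer follow-up.

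The sidedness conflict is part of the same repair: 80 events in total fit one-sided 0.05, whereas the two-sided 0.05 test as written needs about 102.

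**What to change.** 1. Restate the hypotheses. H0: 3-year DFS difference (SLNB minus SLNB + PL) ≤ -8 percentage points. H1: difference > -8 percentage points.
2. Conclude non-inferiority only if the lower limit of the planned 95% CI of the 3-year DFS difference lies above -8 points.
3. State that a non-significant log-rank test is not evidence of non-inferiority.
4. Name the scale and the one-sided level of the primary analysis, reconcile them with the sidedness and the 40 events per arm, and restate the power. The rule in step 2, on the Kaplan-Meier difference, has about 84-87% power after 20% loss. The hazard-ratio scale with 80 events has about 70% at one-sided 0.025, and about 102 events would be needed for 80%.

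Steps 1 to 3 cost only wording in the protocol and SAP, with no change to patients, visits or data. Step 4 costs more than wording, because it settles the primary analysis and its level. The Trial status section expects the last participant to reach the endpoint in 2028, so there is time to amend before the final analysis. In an open-label trial this should be done without sight of results by arm.

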### Sample size

The primary endpoint of this study is 3-year DFS. According to the results of previous research, patients with stage I endometrial cancer who received laparoscopy had 3-year DFS of 88.6% [18]. It is assumed that the 3-year DFS of the reference group and the experimental group is 88%, and the non-inferior boundary value is 8%. Considering the 20% loss of follow-up rate, 361 subjects need to be included in each group to ensure 80.0% power using a 2-sided log-rank test with a type I error rate of 0.05 to reject the null hypothesis. The total sample size of this study is 722 and the number of outcome events in each group is 40. The sample size calculation was done using the PASS software (version 11.0).

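### The sample-size paragraph's event count, power and two-sided 0.05 do not agree: 40 events per group give 80% log-rank power only at one-sided 0.05, and about 70% at two-sided 0.05

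*Protocol article*

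**What the plan says.** All the design figures stand in the Sample size section of the protocol article.

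- Endpoint: "The primary endpoint of this study is 3-year DFS".
- Assumptions: 3-year DFS of 88% in both groups, a non-inferiority margin of 8%, and 20% loss to follow-up.
- Size, power and test: "361 subjects need to be included in each group to ensure 80.0% power using a 2-sided log-rank test with a type I error", with alpha set at 0.05.
- Events: "The total sample size of this study is 722 and the number of outcome events in each group is 40".

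The Statistical methods section plans Kaplan-Meier curves, a log-rank comparison and an intention-to-treat analysis of all randomized patients. It adds: "The 95% confidence interval of the difference between the two groups will be calculated at the same time". It does not say whether that difference is in 3-year DFS or on another scale.

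On follow-up, Table 1 and the Postoperative investigation section schedule visits for 3 years. The Outcomes section defines DFS as a time to event and does not truncate it at 3 years. The accrual period and cutoff used in the calculation are not given.

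**The concern.** For a non-inferiority test, two-sided 0.05 means one-sided 0.025, and the matching interval is the two-sided 95% one. An event-driven calculation is fixed by margin, alpha and power, so the stated 40 events per group can be checked without knowing accrual. The check returns 40 only if the whole 0.05 is placed on one side.

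The rule that decides the trial depends on which statement is meant:

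- If two-sided 0.05 is meant, the named test has less power than the 80% claimed.
- If one-sided 0.05 is meant, the chance of wrongly declaring non-inferiority is 5%, not the 2.5% that the text implies. The matching interval is then 90%, which does not fit the 95% interval in Statistical methods.

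**Working it through.** **Inputs** (Sample size section): DFS at 3 years 0.88 in both arms; bound 0.88 - 0.08 = 0.80; power 80%; 361 per group; 40 events per group; 20% loss. Allocation is 1:1 (Trial design).

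**1. Margin as a hazard ratio** (proportional hazards)

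HR = ln(0.80)/ln(0.88) = 0.22314/0.12783 = 1.746, so ln HR = 0.557.

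**2. Events needed for 80% power** (Schoenfeld): D = 4(z_α + z_β)²/(ln HR)², with z_β = 0.842

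| Alpha | z_α | Total events | Per group |
|---|---|---|---|
| one-sided 0.05 | 1.645 | 79.7 | 40 |
| two-sided 0.05 | 1.960 | 101.2 | 51 |

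The plan's 40 per group comes back exactly at one-sided 0.05. Solving the other way, 80 events with 80% power imply a one-sided alpha of 0.0495. Freedman's formula gives 83.8 and 106.4 in total, so the choice of formula does not explain the gap. Other readings of the margin at two-sided 0.05 do not give 40 per group either: an 88.6% reference gives 47.5, a risk ratio 60.5, an odds ratio 43 and a relative 8% 62.5.

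**3. Power of the named test at the stated events**: Φ(0.557·√D/2 - z_α)

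With D = 80 and z_α = 1.960: Φ(2.491 - 1.960) = Φ(0.531) = 70.2%.

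**4. Where 361 may come from** (accrual assumed, not documented)

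Take λ = 0.12783/3 = 0.0426 per year, uniform accrual over 3 years and 5 years in total. The average event probability is then 0.138. At one-sided 0.05, 39.84/0.138 = 288.8 per group, and 288.8/0.8 = 361.0. Both stated figures are recovered. The same schedule at two-sided 0.05 gives about 458-459 per group. The figure 361 does not settle sidedness by itself: 3-year accrual and 6 years in total, two-sided, gives about 364, but that needs about 51 events per group. The stated 40 is what points to one-sided 0.05.

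**5. Events and power if DFS is censored at 3 years** (conditional)

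| Loss pattern | Total events | Per group | Power, two-sided 0.05 |
|---|---|---|---|
| all 20% lost at entry | 2 × 288.8 × 0.12 = 69.3 | 34.7 | 64% |
| 20% lost evenly over 3 years | 2 × 361 × 0.1078 = 77.8 | 38.9 | 69% |
| no loss | 2 × 361 × 0.12 = 86.6 | 43.3 | 74% |

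Forty events among 288.8 patients would need about 3.5 years' mean follow-up: -ln(1 - 40/288.8)/0.0426 = 3.5.

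**6. Same 722 patients, difference in 3-year DFS against -8 points, one-sided 0.025**

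- All loss at entry: SE = √(2 × 0.88 × 0.12/288.8) = 0.0270. Power = Φ(0.08/0.0270 - 1.960) = 84.1%.
- Even loss (Greenwood): SE = 0.0256, power 87.7%.

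Simulation (4,000 runs) gave 84.4% and 87.5% for this test, and 64.6% and 68.7% for the log-rank non-inferiority test at one-sided 0.025. The proportion-based formula would have asked for 260 per group, or 260/0.8 = 325 with loss. It is therefore not the calculation that produced 361.

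**The case against.** The strongest reply is that the trial may be large enough. The margin is set in points of 3-year DFS, and Statistical methods promises a 95% interval of the difference. If that is the Kaplan-Meier difference at 3 years, power is about 84-88%, better than claimed. This stands. A reader might infer from the log-rank figures that the design delivers only 64-70% and that a truly non-inferior operation would fail about one time in three. The documents do not support that as a general statement: it holds only for a hazard-ratio test at two-sided 0.05, and no section mentions a hazard-ratio interval. The reply does not rescue the paragraph, which names the log-rank test.

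A second reply concerns follow-up. The 64% figure is a worst case in which every lost patient contributes no time, whereas Kaplan-Meier and intention-to-treat analysis keep patients until censoring. A reader might also infer that 40 events is simply wrong and should be 35-39. That too goes further than the documents, because no censoring rule or cutoff is given. Under the assumed schedule in step 4 of the working, 40 is a correct output. If events after year 3 counted, with a 3-year minimum and an assumed 3 to 6 years of uniform accrual, 289 per arm would yield about 100-129 events and 80-89% power at two-sided 0.05. The documents do not plan this, and it would not agree with the stated 40, but it shows that the expected count depends on inputs not given.

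**Conclusion.** The point holds in this form: for the log-rank test that the Sample size section names, two-sided 0.05, 80.0% power and 40 events per group are mutually inconsistent. The event count fits one-sided 0.05. At two-sided 0.05 the power is about 70%, and 80% would need about 51 events per group. This rests only on the stated DFS rates, the margin and proportional hazards; no accrual assumption is needed.

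The figures of 35-39 events per group and 64-69% power are conditional on censoring at 3 years with 20% loss. That the original calculation was one-sided with events counted beyond year 3 is a plausible reconstruction, not something that the documents show. Nor is it shown that 722 patients are too few. The text needs correcting because the choice between the readings changes either the stated power or the rule for declaring non-inferiority.

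**What to change.** Keep 722. Name one primary non-inferiority test, give its alpha and the matching interval, and restate power and events. Two routes are open:

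- **(a)** Use the Kaplan-Meier difference in 3-year DFS, margin -8 points, two-sided 95% interval (one-sided 0.025), with power of about 84-88%. This agrees with the endpoint, the scale of the margin and the 95% interval already planned.
- **(b)** Keep the log-rank (hazard-ratio) test with margin 1.746. Then state either one-sided 0.05 with a 90% interval and 80% power at 80 events, reconciled with the 95% interval in Statistical methods, or two-sided 0.05 with about 70% power at 80 events.

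Under either route, state the accrual, follow-up and cutoff assumption behind the event count. If DFS is censored at 3 years, give about 35-39 events per group.

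The cost is a corrected paragraph and no added patients. Route (a) also changes the named primary test, so it should be recorded as an amendment before outcome data are examined. The Trial status section expects the last primary-endpoint assessment in 2028. Holding to the log-rank test at two-sided 0.05 with 80% power would instead need about 102 events. That means about 918 patients on the assumed 3-year accrual and 5-year total, or about 1,054 if each patient contributes exactly 3 years (both with 20% loss). The correction does not require this.

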### Visit procedures

Follow-up will be conducted at each center. Written informed consent must be obtained before protocol-related procedures (See Table 1).

**Table 1 Tab1:** Study procedures and baseline and/or follow-up assessments

	**Inclusion visit**	**Surgery procedure**			**Postoperative Visit**	**Follow-up Visits**
	Up to 30 days to surgery				30 days(± 7 days)	1^st^year-3^rd^ year every 3 month (± 14 days)
**Inform consent**	x		RANDOMIZATION			
**Screening for eligibility**	x					
**Medical history**	x					
**Physical exam**	x				x	x
**Gynecological examination**	x				x	x
**PS-ECOG**	x				x	x
**Tumor assessment**	x				x^b^	x^b^
**Blood examination, liver and renal function, ECG**	x				x	x
**Chest X-ray or Chest CT**						
**Upper abdominal CT**	x					x^c^
**Pelvic MRI**	x					x^c^
**Endometrial diagnostic curettage pathology**	x					
**Surgery approach (laparoscopic or robotic)**		x				
**SLN mapping and biopsy**		Arm A & B				
**Histological examination**		x				
**TH + BSO**		x				
**PLN dissection**				Arm B		
**paraaortic lymph node resection**		x^a^		x^a^		
**Adverse Events (CTCAE V3.0)**					x	x
**Questionnaires (EORTC QLQC30; EORTC QLQ-CX24)**	x					x

*ECG* Electrocardiogram, *PS-ECOG* Performance Status-Eastern Cooperative Oncology Group, *CT* Computed Tomography, *MRI* Magnetic Resonance Imaging

^a^ See “Additional instructions” from “Operation procedures” section

^b^ If necessary

^c^ Upper abdominal CT and pelvic MRI will be done 6 months after the initial treatment, and if necessary within three years

#### Preoperative investigation

Diagnostic curettage of endometrium can be defined as one of the following pathological types: Endometrioid adenocarcinoma; cancerization.

The following examinations are to be completed within 30 days before operation:

Chest X-ray or Chest CT examinationUpper abdominal CT and Pelvic MRI (PET-CT and/or ultrasound can also be done if there are clinical indications); ECG

The following steps are to be completed 30 days before the operation:

Sign written informed consentRecord all drugs used currently and in the past 12 weeks (including prescription drugs, over-the-counter drugs, vaccines, vitamins, or proprietary Chinese medicines)Complete the “quality of life” assessmentComplete physical and pelvic examinationsPS-ECOGRecord weight (kg) and height (cm)Perform standard preoperative laboratory examination of each institutionPerform serum pregnancy test (if necessary)Perform biochemical tests including creatinine, bilirubin, albumin, alkaline phosphatase (ALP), aspartate aminotransferase (AST), and alanine aminotransferase (ALT)Record whole blood cell count

#### Operative investigation

This visit will perform the following process:

Surgery according to random results;Record intraoperative and postoperative information (including operation, histopathological results, intraoperative complications, blood transfusion and other special conditions during operation).

#### Postoperative investigation

The following interviews are planned at 1 month, then every 3 months after surgery for 3 years:

Complete the quality of life assessment form (QLQ-C30, QLQ-CX24);Review PS-ECOG;Physical exam and pelvic examination, tumor assessment (if necessary)Record the whole blood cell count and biochemical indexesAdverse event assessment (Common Terminology Criteria for Adverse Events (CTCAE) V3.0);Postoperative pelvic B-ultrasound is used to determine whether there is a lymphocyst. If the patient has symptoms such as swelling and pain in the lower extremities, color Doppler ultrasound in the lower extremities will be used to assess the presence or absence of DVT. The development of lymphedema is investigated and evaluated by measuring the circumference of the legs and combining with the methods of pelvic ultrasound.

In addition, upper abdominal CT and pelvic MRI will be done 6 months after the initial treatment, and if necessary within three years.

